# Supporting People Who Have Lost a Close Person by Bereavement or Separation: Protocol of a Randomized Controlled Trial Comparing Two French-Language Internet-Based Interventions

**DOI:** 10.2196/39026

**Published:** 2022-06-23

**Keywords:** internet-based interventions, grief, bereavement, separation, divorce, identity, digital health, mental health, psychotherapy

## Abstract

**Background:**

Internet-based interventions (IBIs) are as efficient as face-to-face psychotherapy for a variety of mental health disorders, including complicated grief. Most evidence stems from guided IBIs. However, recent research indicates that the benefit of guidance is lower in more interactive IBIs. As such, providing guidance only to people requiring it (guidance on demand) appears a cost-effective solution. This is particularly important to develop given the recent rise in grief symptoms in the context of the COVID-19 pandemic. This paper presents the protocol of a randomized controlled trial comparing the efficacy and adherence rate of 2 IBIs for grief-related symptoms after the loss a close one following death or romantic separation, using a guidance on demand framework. LIVIA 2.0 was developed based on theoretical and empirical findings on grief processes and IBIs, and it will be compared to LIVIA 1 that has already demonstrated its efficacy.

**Objective:**

Our main hypotheses are that LIVIA 1 (control condition) and LIVIA 2.0 (experimental condition) increase participants’ well-being and decrease their distress at posttest and at follow-up, that LIVIA 2.0 is more efficient than LIVIA 1 for all outcomes, and that LIVIA 2.0 has less dropouts than LIVIA 1.

**Methods:**

Outcomes will be assessed at pretest, posttest (12 weeks later), and follow-up (24 weeks later). We will recruit 234 participants through a variety of means, including social media and contacts with the press. Primary outcomes are grief symptoms, depressive symptoms, and eudemonic well-being. Secondary outcomes are anxiety symptoms, grief coping strategies, aspects related to self-identity reorganization, and program satisfaction. LIVIA 2.0 participants will additionally undergo a weekly mood and grief symptom monitoring, allowing us to explore the short-term efficacy of the sessions.

**Results:**

The creation and development of the content of LIVIA 2.0 was completed during the first phase of the project. Participant recruitment will begin in May 2022 and will last until January 2023.

**Conclusions:**

This study will emphasize the relevance of the innovations included in LIVIA 2.0 regarding the efficacy and dropout rate of IBIs for grief symptoms and will allow investigations on how these changes impact the demand for guidance. In the current postpandemic times, developing and assessing IBIs targeting grief symptoms are particularly critical given the rise in grief-related symptoms.

**Trial Registration:**

clinicaltrials.gov NCT05219760; https://tinyurl.com/3dzztjts

**International Registered Report Identifier (IRRID):**

PRR1-10.2196/39026

## Introduction

### Background

Internet-based interventions (IBIs) offer numerous efficient prevention and treatment programs for a variety of psychological difficulties [1,2]. Generally based on methods originating from empirically supported face-to-face psychological interventions for people reporting complicated grief symptoms [3,4], IBIs for grief-related symptoms are also effective [5,6].

Offering guidance to participants is one of the most commonly cited means to improve IBI effectiveness [7], including grief-related symptoms [5]. However, recent evidence indicates that the benefits of guidance are lower in more interactive internet interventions [8]. Moreover, when given the choice, not all participants request guidance. Additionally, the efficacy of guidance on demand is similar to standard weekly guidance [9-11]. Finally, including specific and individualized principles, such as the Motive-Oriented Therapeutic Relationship (MOTR), in the guidance appears feasible and useful for IBIs [12,13]. Thus, MOTR-based guidance on demand appears as a cost-effective alternative to mandatory guidance. Other elements can also improve adherence rate and efficacy: (1) using automated reminders [14]; (2) providing interactivity in the tasks and exercises [15-18]; (3) promoting personal resources to cope when problematic experiences arise [19,20]; (4) tailoring the intervention to the participant’s characteristics and timing the content in accordance with the participant’s characteristics [21-24].

LIVIA 2.0 was developed as an alternative IBI to LIVIA 1, the original program, for grief-related symptoms after bereavement or separation [25], which was tested in German via a randomized controlled trial (RCT) [26] and in French via a noncontrolled trial [27]. Indeed, fundamental research has pointed to the many similarities between these kinds of losses [27,28]; moreover, studies on LIVIA 1 have proved that the same intervention can be provided to both populations [26,29]. LIVIA 2.0 implements different factors to improve patient adherence and program efficacy. Specifically, it includes automated emails, increased interactivity (quizzes, video files, and audio files), personal resource assessment and promotion, and the freedom to choose the session order combined with an individualized recommendation. The content is based on the Dual Process Model (DPM) of bereavement recovery and proposes an oscillation process mimicry [30,31] with an alternation of loss-focused and restauration-focused sessions. Finally, LIVIA 2.0 includes a module focused on identity and memory processes that play a key role in adapting to loss [32,33] as well as novel emotion regulation tools [34,35].

In detail, the development of LIVIA 2.0 and its innovations were based on the theoretical and empirical literature about grief and romantic dissolution. On the theoretical level, we relied on one of the most influential models of coping with loss, the DPM of Coping with Bereavement [30,31]. According to it, after loss, instead of going through consecutive phases, people oscillate between a focus on the loss and a focus on the restauration from the loss. This model postulates that oscillation is a natural and necessary movement to cope with loss. Moreover, DPM-based interventions are more efficient than classic ones [36]. Hence, LIVIA 2.0 imitates the oscillation process by alternating between loss- and restauration-focused sessions. Additionally, LIVIA 2.0 integrates recent loss-related empirical findings into its content and exercises. For example, the Emotion module proposes self-compassion exercises, as self-compassion has been shown to predict better grief recovery [37,38]. Moreover, LIVIA 2.0 includes a newly developed module based on empirical cognitive psychopathological knowledge and focused on identity processes, which play a key role in adaption to bereavement [32,33]. Addressing identity factors, such as fostering an independent sense of identity by focusing on adaptive specific autobiographical memories and future projections, could improve existing cognitive-behavioral programs for grief.

LIVIA 2.0 also integrates recent developments in IBIs [16,20]. First, a series of changes are designed to improve participant autonomy by sending automated emails [14], providing individualized recommendations about the order in which to complete the modules [22], promoting and encouraging the use of personal resources [20], and augmenting the interactivity of the website [15-18]. Finally, the emails exchanged with the participants within the guidance on demand framework will be based on the MOTR [12].

### Objectives

Our main hypotheses are the following: (1) LIVIA 1 and LIVIA 2.0 increase participants’ well-being and decrease their distress at posttest and follow-up. (2) LIVIA 2.0 is more efficient than LIVIA 1 for all outcomes. (3) LIVIA 2.0 has less dropouts than LIVIA 1.

Moreover, we will conduct the following exploratory analyses. First, we will compare the guidance requirements of the participants (ie, number of participants requiring guidance and number of exchanged emails) in LIVIA 2.0 with those of the LIVIA 1 participants and explore which session triggers more requests for guidance. Second, we will examine in LIVIA 2.0 the short-term effectiveness of each module on the participants' weekly moods, feelings of loneliness, and grief symptoms. Third, we will compare participant satisfaction in the 2 versions of LIVIA. Fourth, we will explore the role of multiple measures (attachment style, type of loss, interpersonal closeness to the lost person, and symptom severity) as moderators of the program’s effectiveness. Finally, we will investigate the semantic content of the responses to the LIVIA 2.0 exercises [39] to explore its relationship with improvement over the evaluation period.

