### Design and Procedure

This study is a monocentric, single-blinded, 2-arm RCT comparing the efficacy of 2 versions of an IBI—namely LIVIA 1 and LIVIA 2.0—aimed at relieving distress and augmenting the well-being of people suffering from prolonged grief symptoms. There will be three measurement points: a pretest (T0), posttest (T1), and follow-up (T2). The flowchart of the study design is presented in Figure 1.

This self-help intervention is embedded in a larger project on life-span vulnerabilities and strengths conducted by the LIVES Centre [40].

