### Study Conditions

#### LIVIA 1: Control Condition

LIVIA 1 is a self-help intervention for coping with prolonged grief symptoms after the death of a loved one or romantic separation/divorce, developed at the University of Bern by Brodbeck and colleagues [25]. Participants are encouraged to work through 1 session per week and complete the exercises provided. Each session takes approximately 60 minutes to complete. The sessions must be completed in the prescribed order. Details of the session contents can be found elsewhere [25].

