### Assignment of Interventions

To assign participants to the LIVIA 2.0 (experimental) or LIVIA 1 (control) condition, we will use the randomization module in REDCap (Research Electronic Data Capture [41,42]), which will automatically generate a 1:1 randomization. We will apply a single-blinded randomization strategy stratified according to the gender and loss type (bereavement vs separation) of the participants. Due to the nature of the study, double-blinded randomization is not possible.

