#### Eligibility Criteria

Participants meeting all the following inclusion criteria will be eligible for the study: (1) have experienced bereavement or separation, (2) either events must have happened more than 6 months prior to participating in the study, (3) feel the need for support to cope with the loss (a diagnosis of complicated grief is not necessary), (4) aged 18 years or older, (5) have regular access to the internet, (6) fluent in French, and (7) have approved the informed consent form.

The presence of any of the following exclusion criteria will preclude individuals from participating in the study: (1) moderate to acute current suicidality (Suicidal Ideation Attributes Scale score>19] [44,45]) (Note that participants having a Suicidal Ideation Attributes Scale score between 13 and 19 will undergo a telephonic interview to accurately assess their suicidal risk and will be excluded from the study if the risk is assessed as important [46]), (2) severe psychological or somatic disorders that need immediate treatment, (3) concomitant psychotherapy, (4) prescription or change in dosage of psychoactive drugs in the month prior to or during the self-help intervention, (5) inability to follow the study procedures (eg, due to comprehension problems), and (6) enrolment of the investigator, their family members, employees, and other dependent people.

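### Main hypothesis 1 credits both programmes with improvement, but with two active arms and no untreated comparator, within-arm change cannot be separated from natural course or possible regression to the mean

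*Protocol article*

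**What the plan says.** The Objectives section, and the Objective paragraph of the Abstract, list three main hypotheses. The first is that both programmes raise participants' "well-being and decrease their distress at posttest and follow-up". The second is that "LIVIA 2.0 is more efficient than LIVIA 1 for all outcomes". The third is that LIVIA 2.0 has fewer dropouts.

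Design and Procedure describes a "2-arm RCT comparing the efficacy of 2 versions of an IBI". The control is itself a treatment: "LIVIA 1 is a self-help intervention for coping with prolonged grief symptoms after the death of a loved one or romantic separation/divorce" (LIVIA 1: Control Condition). Assignment of Interventions uses the REDCap module, "which will automatically generate a 1:1 randomization", between these two programmes. No untreated, waitlist or attention-control arm is described.

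Under Eligibility Criteria, participants must "feel the need for support to cope with the loss", the loss must be more than 6 months old, and no diagnosis is required. Outcomes are measured at baseline, 12 weeks and 24 weeks.

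The sample size (Sample Size) and the mixed model (Statistical Analysis) are both directed at LIVIA 2.0 versus LIVIA 1. Strengths and Limitations names self-selection by education and gender, varied paths through LIVIA 2.0, and concurrent psychotherapy that cannot be verified. It does not name natural recovery, regression to the mean or the lack of an untreated arm.

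**The concern.** Hypothesis 1 is a causal statement about each programme, and the design has no contrast that isolates it. Change from baseline within an arm is the sum of the programme effect, the natural course of grief over the period, and any regression to the mean in people who enrol at a time when they feel in need of help. Randomisation makes the last two comparable between arms. It does not remove them from either arm.

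The protocol's own defence shows the gap. Strengths and Limitations answers the worry about concurrent psychotherapy by noting that randomisation should make the bias equal in the two arms. That protects hypothesis 2. For hypothesis 1, a bias that is equal in both arms enters both pre-post changes in full.

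At stake is what may be concluded about each programme on its own. The sample size section expects only small differences between the programmes, so a null result on hypothesis 2 is a realistic outcome. Hypothesis 1 would then remain as a listed main hypothesis that the trial cannot test as worded.

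**Working it through.** **The plan's own figure.** Sample Size gives *f* = 0.1, alpha .05, power 0.8 and N = 164 for a within-between interaction. With 2 groups and 3 time points from the document, and an assumed correlation of 0.5 and sphericity:

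- noncentrality = f² × N × m / (1 − ρ) = 0.01 × 164 × 3 / 0.5 = 9.84
- df = (2 − 1)(3 − 1) = 2 and (164 − 2)(3 − 1) = 324
- power = 0.805, and 164 is the smallest even N that reaches 0.80.

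For dropout, 164 / 0.7 = 234.3, against the stated 234. Both figures reproduce. They concern the difference between programmes (hypothesis 2) and do not bear on hypothesis 1.

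**Illustration for hypothesis 1.** Suppose neither programme has any effect and every participant's expected improvement is non-specific drift *d*, in baseline SD units.

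- Numbers per arm: 164 / 2 = 82 and 234 / 2 = 117 (from the document, 1:1 allocation).
- Pre-post correlation ρ = 0.5 and *d* = 0.1 to 0.4: assumptions, not in the document.
- SD of change = √(2(1 − ρ)) = √(2 × 0.5) = 1, so the standardised change equals *d*.
- Paired t-test, two-sided .05, noncentrality = d × √n. For example, 0.2 × √82 = 1.81 and 0.2 × √117 = 2.16.
- Participants in the two arms are independent, so P(both arms significant) = P(one arm significant)².

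| Drift (SD) | One arm, n = 82 | Both arms, n = 82 | One arm, n = 117 | Both arms, n = 117 |
|---|---|---|---|---|
| 0 | 0.05 | 0.003 | 0.05 | 0.003 |
| 0.1 | 0.146 | 0.021 | 0.189 | 0.036 |
| 0.2 | 0.432 | 0.187 | 0.574 | 0.329 |
| 0.3 | 0.766 | 0.586 | 0.896 | 0.802 |
| 0.4 | 0.947 | 0.897 | 0.990 | 0.980 |

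The figures are for one outcome at one time point. Hypothesis 1 speaks of both programmes, so the both-arms columns are the relevant ones. Requiring several outcomes and both time points as well cannot raise them.

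**Sensitivity to the correlation.** With ρ = 0.7, the SD of change is √0.6 = 0.775 and the both-arms probabilities rise to 0.045, 0.406, 0.872 and 0.992 (n = 82) for drift of 0.1, 0.2, 0.3 and 0.4 SD.

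**Reading.** The nominal error rate holds only at zero drift. For any fixed drift above zero, a larger sample makes the wrong attribution more likely, so no sample size cures the problem.

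**The case against.** Four points on the other side deserve weight.

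*LIVIA 1 is presented as already shown to be effective* (Abstract, Background; Discussion). If LIVIA 2.0 beats a comparator that works, the randomised contrast supports LIVIA 2.0 indirectly. This stands in part. The evidence lies outside this trial, and by the Introduction's account the controlled trial was in German while the French study had no control. It does not cover LIVIA 2.0, and it gives LIVIA 2.0 no support if hypothesis 2 is null.

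*The 6-month criterion may reduce natural recovery.* It may, but it does not exclude it over a further 24 weeks. Regression to the mean is likewise plausible rather than shown, since entry uses a felt need and no cut-off on an outcome scale.

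*A reader might infer that hypothesis 1 would probably be confirmed even with inert programmes.* The documents do not support that. They give no drift. At 0.2 SD and a correlation of 0.5, both arms are significant with probability only 0.19 or 0.33, and at 0.1 SD with 0.02 or 0.04. The inference needs the larger assumed drifts.

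*A reader might also infer that the plan would declare both programmes effective on pre-post significance, or that hypothesis 1 uses up part of the Bonferroni correction.* Neither is stated. No conclusion rule of that kind appears, the planned model is framed as LIVIA 2.0 against LIVIA 1, and Statistical Analysis does not define the family of tests that Bonferroni covers.

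None of these points supplies the missing comparator for hypothesis 1.

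**Conclusion.** The concern holds as a mismatch between a causal main hypothesis and a design that cannot identify it. This part needs no assumption: with two active arms, within-arm change is not an estimate of programme effect. How often a false attribution would follow depends on drift and correlation that the documents do not give. At a correlation of 0.5, for one outcome at one time point, the probability that both arms are significant runs from about 0.02 (0.1 SD, 82 per arm) to 0.98 (0.4 SD, 117 per arm).

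The reach is limited. Hypotheses 2 and 3 are randomised contrasts and are unaffected, as are the sample size, the allocation and the data collection. The point concerns what may be claimed for each programme alone.

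**What to change.** - In the Objectives and the Abstract, restate hypothesis 1 as a descriptive aim: estimated within-arm change at posttest and follow-up with confidence intervals, stated not to be attributable to the programmes.
- Keep hypothesis 2 as the confirmatory efficacy question.
- Add to Strengths and Limitations that there is no untreated arm, so natural course and possible regression to the mean cannot be separated from programme effect.

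This costs wording only, with no new participants, arm or data. The downside is that one headline claim is given up. Keeping the causal wording would need an untreated or waitlist arm, which is a different trial.

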The feelings of loneliness will be measured with the University of California Los Angeles Loneliness Scale [62,63] contains 10 positive (eg, “I feel in tune with the people around me”) and 10 negative (eg, “I lack companionship”) items. Participants will respond to each item using a 4-point scale (1=never to 4=often).

Program satisfaction will be measured with a translated version of the Client Satisfaction Questionnaire adapted to IBIs [64]. The questionnaire will assess satisfaction with the theoretical content, practical content (exercises), structure, design, and overall assessment of the intervention. It contains 15 items rated with a scale ranging from 1 (no) to 4 (yes) and 4 open-ended questions.

Additionally, we will monitor the mood of the LIVIA 2.0 participants on a weekly basis using a single item: “How would you describe your current mood” on a scale ranging from 0 (very bad*)* to 6 (very good). Moreover, we will monitor weekly grief and solitude symptoms on a scale ranging from 0 (strongly disagree) to 7 (strongly agree) with the following items: “During the past 24 hours, (1) I have felt negative emotions; (2) I have had negative images or thoughts; (3) I felt blocked in my behavior (what I do, my activities); (4) I felt lonely; (5) I had a very clear vision of myself.” We will also assess the linguistic behaviors in the exercises of LIVIA 2.0 where the participants are required to describe a loss-related situation. More specifically, we will analyze indicators of verbal immediacy (use of first-person pronouns and present-tense words) and so-called “we-talk” (first-person plural pronouns [39]). Finally, we will assess the degree of guidance required in each group (number of participants requiring guidance and number of emails exchanged).

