### Statistical Analysis

Primary analyses will be performed using SPSS (IBM Corporation) and R (R Foundation for Statistical Computing) after the participants complete the study. Primary follow-up analyses will be conducted 3 months later. Intermediate analyses during data collection will be done. We will perform intention-to-treat analyses [70]. We will develop multilevel mixed effects models with repeated measures data in SPSS to evaluate the efficacy of LIVIA 2.0 compared to LIVIA 1 and the stability of the effects. These models have the advantages of considering the dependency of the data and accounting for the correlation of repeated measures within individuals. Moreover, they rely on all available data of every participant and estimate parameters of missing values [71].

We will explore the potential moderating effect of different variables on the intervention effects by conducting analyses of covariance for repeated measures. To explore the short-term efficacy of each module, we will use multilevel modeling whereby each participant’s monitoring data are nested within participants. These analyses will be conducted with Mplus [72] or R. Additionally, we will analyze qualitatively the satisfaction questionnaire using the thematic content analysis method [73]. Finally, we will analyze the semantic content of the exercises included in LIVIA 2.0 [39] and test if some categories (eg, “we-talk”) are associated with the efficacy of the program. We will rely on a significance level of a 2-sided *α*=.05 or smaller. We will use the Bonferroni correction to adjust for multiple testing.

To handle missing data and dropouts, we will conduct the analyses relying on the intention-to-treat paradigm. We will first analyze the magnitude of missing data, explore the missing data patterns, and determine the pattern of missing data (missing completely at random, missing at random, and not missing at random). If the missing mechanism is missing at random, we will use multilevel regression analyses, which allow for nonindependent observations and for different numbers of measurement points per participant and are thus less sensitive to missing data [71].

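### Main hypothesis 2 claims superiority on all outcomes, which conflicts with the three-primary hierarchy and leaves the Bonferroni correction tied to no stated claim; at .05/3 the power is about 67%, not 80%

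*Protocol article*

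**What the plan says.** - **Hypothesis.** The Objectives section opens its list with "Our main hypotheses are the following". The second item is that "LIVIA 2.0 is more efficient than LIVIA 1 for all outcomes". The Abstract (Objective) repeats it. Neither place limits the claim to the primary outcomes.
- **Hierarchy.** The Abstract (Methods) states: "Primary outcomes are grief symptoms, depressive symptoms, and eudemonic well-being". It continues: "Secondary outcomes are anxiety symptoms, grief coping strategies, aspects related to self-identity reorganization, and program satisfaction". The Measures section keeps the two tiers under separate headings and adds loneliness to the secondary tier.
- **Exploratory label.** Satisfaction and the degree of guidance required both appear under Secondary Outcome Measures. The Objectives section lists both comparisons among the exploratory analyses; for satisfaction it says "Third, we will compare participant satisfaction in the 2 versions of LIVIA".
- **Error control.** Statistical Analysis says "We will rely on a significance level of a 2-sided" alpha of .05 or smaller, and then "We will use the Bonferroni correction to adjust for multiple testing".
- **Sample size.** The Sample Size section uses a repeated-measures ANOVA within-between interaction, a probability level of 0.05, power 0.8 and f = 0.1. This gives 164 participants, raised to 234 for 30% dropout.

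**The concern.** A primary/secondary split tells the reader which results carry the confirmatory claim. A main hypothesis of superiority on every outcome says something different, and the article contains both. Satisfaction and guidance demand show the conflict most plainly: they fall within all outcomes by their heading and outside the confirmatory set by the Objectives section.

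The correction cannot settle which statement governs, because its role depends on how the hypothesis is read:

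- If superiority must be shown on every outcome, the claim is a conjunction. Each test can run at .05, and Bonferroni only costs power.
- If each outcome is claimed separately, Bonferroni is valid, but the family is all outcomes rather than three.
- If only the three primary outcomes are confirmatory, the divisor is three, but that is not what hypothesis 2 says.

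Two things are at stake. The same grief p-value of .010 succeeds with a divisor of 3 (.0167) and fails with a divisor of 10 (.0050). And whenever Bonferroni applies to more than one outcome, the 80% power in the Sample Size section is not the power of the test that will be read.

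**Working it through.** **Inputs.** From Sample Size: f = 0.1, alpha .05, power .80, N = 164, dropout 30%. From Design and Procedure: two arms (k = 2) and three measurement points (m = 3). Assumed, because the article does not give them: correlation between repeated measures ρ = 0.5 and sphericity ε = 1.

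**Step 1. Reproduce the plan's figure.** For the within-between interaction:

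- λ = f² × N × m / (1 − ρ) = 0.01 × 164 × 3 / 0.5 = 9.84
- df1 = (k − 1)(m − 1) = 2; df2 = (N − k)(m − 1) = 162 × 2 = 324
- Power at alpha .05 = .805; at N = 162 it is .7998

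So 164 is the smallest even N that reaches 80%. Other assumptions do not give it: ρ = 0.3 needs 228, ρ = 0.7 needs 98, and two measurements at ρ = 0.5 need 200. Dropout: 164 / 0.7 = 234.3, which matches the stated 234. The arithmetic is sound at an undivided .05.

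**Step 2. Same test, same N, Bonferroni alpha.** The 2-df interaction already covers both post-baseline times, so each outcome contributes one test.

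| Family | Alpha | Power at N = 164 | N for 80% |
|---|---|---|---|
| One test (as sized) | .0500 | .805 | 164 |
| 3 primary outcomes | .0167 | .665 | 212 (303 after dropout) |
| 10 outcomes (illustrative) | .0050 | .506 | 264 (378 after dropout) |

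The count of 10 is mine: 3 primary, anxiety, 2 coping orientations, 3 identity scales and loneliness. The article does not state it, and other counts are possible.

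**Step 3. Does the loss depend on ρ?** Hardly. Any two-sided normal test calibrated to 80% at .05 has mean shift 1.960 + 0.842 = 2.802. At .05/3 the critical value is 2.394, so power is Φ(2.802 − 2.394) = .66.

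**Step 4. Holm against Bonferroni on the three primary outcomes.** Holm compares the ordered p-values with .05/3 = .0167, .05/2 = .025 and .05, stopping at the first failure. Every Bonferroni rejection is also a Holm rejection, and family-wise error is still at most .05. I simulated three normal tests, each with 80% power at .05 and with pairwise correlation 0.5 (assumed):

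| | Bonferroni | Holm |
|---|---|---|
| Average power per outcome | .66 | .74 |
| All three significant | .42 | .59 |

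For all three significant, correlation 0.3 gives .36 against .55, and correlation 0.7 gives .48 against .64. The chance of at least one success is identical, because the first Holm step is the Bonferroni step. The gain assumes real effects on all three outcomes.

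**The case against.** The strongest reply is that hypothesis 2 is a directional expectation in ordinary language, not a decision rule. The primary and secondary headings remain in force, so the three primary outcomes can be taken as the confirmatory family. The exact family for a Bonferroni correction is commonly left to a statistical analysis plan, which is not shown. Bonferroni is a valid method, and wording that allows an alpha below .05 is compatible with it.

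Much of this stands. A reader might infer any of the following, and the article supports none of them:

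- *Hypothesis 2 abolishes the hierarchy.* It does not. The tiers are still printed, so the two statements conflict and neither cancels the other.
- *The threshold falls to about .0024.* That is .05/21, a count the article never gives. It also counts time points separately, which does not fit a 2-df interaction test covering both. An undefined family alone is missing detail and no finding.
- *A false superiority claim is likely.* That presumes no correction, whereas the article commits to one.
- *Weekly mood and language markers must be tested between arms.* The article says "Additionally, we will monitor the mood of the LIVIA 2.0 participants on a weekly basis using a single item" and treats both as exploratory. Their place under the secondary heading is loose, but nobody would expect a between-arm test.
- *Dropout is an orphan claim.* It has its own hypothesis, and its absence from a list of questionnaires contradicts nothing.

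On power, one could add that the planned mixed models use partial data from dropouts. If all 234 gave complete data, power at .0167 would be .847. But the article itself expects 30% dropout and sizes on 164, so 67% is the figure comparable with its 80%.

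The reply does not remove the published contradiction between a main hypothesis on all outcomes and the outcome hierarchy, the double label on satisfaction and guidance demand, or a stated power that ignores the stated correction.

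**Conclusion.** The point holds as a conflict of wording with a measurable consequence. Hypothesis 2 disagrees with the primary/secondary split and with the exploratory label on satisfaction and guidance demand, so the Bonferroni sentence cannot be attached to a definite claim. On the mildest multiple-outcome reading, power at 164 is about 67% rather than 80%. The ten-outcome figure of about 51% is an illustration only. The 67% rests on f = 0.1, three measurements, correlation 0.5 and ε = 1, the combination that reproduces the 164. The sample-size arithmetic is correct as stated; the mismatch lies in the alpha it uses. The Holm figures also assume real effects on all three outcomes and a correlation between them.

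**What to change.** 1. **Abstract (Objective) and Objectives.** Limit confirmatory hypothesis 2 to grief symptoms, depressive symptoms and eudemonic well-being, with superiority claimed separately for each. Name one test per outcome: the group-by-time interaction used for sizing, with direction read from the estimated arm differences.
2. **Statistical Analysis.** Replace the Bonferroni sentence with the Holm procedure across these three tests at a family-wise two-sided .05.
3. **Secondary outcomes.** Report anxiety, coping, identity and loneliness with 95% confidence intervals as supportive results.
4. **Satisfaction and guidance demand.** Call both exploratory wherever they appear.
5. **Sample Size.** State that the 80% is per outcome at an unadjusted .05, and that it is about 67% at .05/3.

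Hypothesis 3 on dropout and the phrase allowing a smaller alpha need no change.

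**Cost.** Wording only, with no added data or participants. Holm loses nothing against Bonferroni on the same three tests. There are two downsides: secondary outcomes no longer carry a confirmatory claim, and the published power looks less favourable. Restoring 80% at .05/3 would take 212 evaluable participants (303 after dropout), but that is a separate decision. The article reports that no data had been collected at submission, so the rule could be fixed before results were seen.
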